#### Piecewise Linear Regression Analysis

To supplement the visual analysis, we will conduct piecewise linear regression analyses (PLMs) using the *scan* package [77]. PLM is an approach to analyzing time-series data that are segmented into phases, including SCEDs [77,78]. The PLM model calculates 4 parameters (intercept, trend, level, and slope) separately for data from each phase, allowing for a comparison between phases. In this case, *intercept* refers to the performance at the start of the study, *trend* effects refer to the continuous increase in the behavior over time, *level* effects refer to the constant and instant effect of the intervention, and *slope* effects refer to the change in continuous increase initiated by the intervention.

Using the PLM, we will construct a linear model for each individual patient, including a *P* value, *R*^2^ effect size, and beta weights for trend, level, and slope effects. We will use a cutoff of *P*<.05 to determine significant effects.

In SCED I only, we will also construct a multilevel PLM to aggregate single-case findings across all participants included. Aggregation improves the external validity of the findings by providing overall trend, level, and slope effects and allows for the exploration and quantification of moderation effects using random slopes [77]. First, we will include random slopes in the multilevel PLM to examine whether trend, level, and slope effects differ significantly between participants. If this is the case, we will subsequently consider the interactions between body weight, height, stage of change, clinic type, intervention use, trait self-control, and cognitive control as potential moderators of the effect. As there are no existing hypotheses about moderation, we will not use confirmatory *P* values in this analysis but merely report any findings as preliminary and exploratory.

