### Randomization and Blinding

We will randomly assign participants to different baseline, intervention phase B, and follow-up durations in SCED I. All are drawn a priori using the web-based random number generator Research Randomizer [45] with the restriction of having at least 5, 7, and 28 baseline observation days, respectively. In SCED II, phase length will not be randomized as the optimal intervention length will be derived from SCED I. Phase order will not be randomized in both experiments as we are interested in the additive effect of SCT over Google Fit only.

Owing to the nature of the intervention, in which apps are used by participants, it is not possible to blind participants to the phase. The researchers responsible for supporting participants in transferring between phases will not be blinded to the phase for the same reason. Where possible, researchers only involved in data entry, processing, and analysis will be blinded to the phase to improve the reliability of the findings [36].

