### Data Analysis

#### Overview

Data analysis will include both visual and supplementary statistical analyses of the time-series data for both SCED I and II [36,42]. Data analysis will be performed using Microsoft Excel (Microsoft Corp), the web-based Tau-U calculator accessible via Single Case Research [72], and R (version 1.4; R Foundation for Statistical Computing) [73] and separately for the primary and secondary outcomes.

To prepare the data for analysis, we will score the primary outcome of physical activity as the daily average of total activity counts per hour. The secondary outcome of daily self-control will be scored as the daily average of the 4 self-control items. Next, we will use the median average deviation to identify and remove outliers. The median average deviation uses the median to identify scores that deviate 3.5 times from the median as outliers using a 95% CI. It is specifically recommended for use in small-sample studies, including SCEDs [74].

As both experiments collect continuous data that are averaged on a daily level, our missing data approach primarily consists of making full use of data that are available. To illustrate, self-control will be measured in the morning and evening. If the morning data are missing, the afternoon data will be used to calculate the level of self-control for that day. If no data are available on a given day, we will use multiple imputation to impute missing data. Multiple imputation methods have recently been developed specifically for use in SCED studies and have several advantages over other missing data approaches, including retention of collected data, maintenance of the design structure of an SCED, reduction of bias, and the ability to capture and communicate uncertainty regarding imputed scores [75].

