#### Visual Analysis

SCED data are primarily interpreted visually [36]. To do so in this study, physical activity and state self-control data will be presented as a time-series graph, with days on the horizontal axis, physical activity or self-control on the vertical axis, and phase changes presented as vertical lines. As recommended by the What Works Clearinghouse guidelines [44,46], we will consider 6 features to examine within- and between-phase data patterns visually: level, trend, variability, overlap, immediacy, and consistency. The phase contrasts to be compared in SCED I are A versus B (baseline with Google Fit only), B versus C (Google Fit only with Google Fit+SCT), and A versus C (baseline with Google Fit+SCT). The phases compared in SCED II are B versus C (Google Fit only with Google Fit+SCT).

Within phases, *level* refers to the mean of all data points in 1 phase and is used to compare changes between phases [36]. *Trend* is the slope of the best-fitting trend line for all data in a phase and is used to determine trends toward (spontaneous) improvement or decline. *Variability* expresses the SD of data about the trend line and is used to calculate the percentage of overlap between data collected in different phases.

Between phases, *overlap* is the proportion of overlap between data from 2 phases, where less overlap indicates stronger intervention effects. The specific nonoverlap index we will use is the Tau-U summary index [76], which is a family of 4 indexes that calculate nonoverlap in relation to the trend. It is expressed by “the percent of data that improve over time considering both phase nonoverlap and Phase B trend, after control of Phase A trend” [76]. Using Tau-U allows for the exploration of, for example, how much the physical activity of a patient has increased after using the SCIPP app while considering a possible increase in physical activity levels that may have already been initiated by Google Fit during the previous phase.

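### The per-patient piecewise regressions name no serial-correlation term and apply an unadjusted P<.05 to every trend, level and slope effect, without naming the B-to-C change as the key parameter

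*Protocol article*

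**What the plan says.** Under Piecewise Linear Regression Analysis, the model is described by its parameters: "The PLM model calculates 4 parameters (intercept, trend, level, and slope) separately for data from each phase, allowing for a comparison between phases". It is fitted person by person ("Using the PLM, we will construct a linear model for each individual patient"), with a P value, R² and beta weights for trend, level and slope. The decision rule is "We will use a cutoff of *P*<.05 to determine significant effects". The data are one value per patient per day: "As both experiments collect continuous data that are averaged on a daily level". Physical activity and self-control are analysed separately.

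Only the moderator analysis is exempted from confirmatory P values. No adjustment for the number of tests is given for the rest.

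Three other passages bear on the point:
- Study Objectives makes the primary question the effect on physical activity of adding the training app to Google Fit. In design terms that is B to C.
- Visual Analysis states that "SCED data are primarily interpreted visually", and the regression section opens with "To supplement the visual analysis, we will conduct piecewise linear regression analyses (PLMs) using the *scan* package".
- Randomization and Blinding says of SCED I: "We will randomly assign participants to different baseline, intervention phase B, and follow-up durations in SCED I". SCED II phase lengths are not randomised.

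**The concern.** There are two separate problems.

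The first is multiplicity. An A-B-C model has 5 testable coefficients: the initial trend, and a level and a slope change at each of two boundaries. Each is declared at 5%, in each of 6 patients, for each of 2 outcomes. With no coefficient marked as decisive, a reader cannot tell a planned positive result from one of several expected by chance.

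The second is serial correlation. Successive days in one person may well resemble each other. If they do, a plain linear model has standard errors that are too small, and each 5% test rejects more often than 5%.

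With 6 patients per experiment, one or two patients wrongly labelled as showing a significant effect could colour the report.

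**Working it through.** The article derives no power or family-wise error figure, so there is none to reproduce. The check is a simulation of the stated rule when nothing has an effect.

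**Inputs from the article**
- Cutoff P<.05, taken as two-sided; sidedness is not stated.
- 6 patients per experiment and 2 outcomes.
- SCED I minimum phase lengths (Table 1): A 5, B 7, C 28 days.
- Contrasts listed for SCED I: A-B, B-C and A-C. Follow-up is therefore not modelled here as a fourth phase.

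**Assumptions**
- Ordinary least squares with a trend, plus a level and slope change at each boundary.
- AR(1) errors with lag-1 correlation ρ from 0 to 0.6.
- For the two-outcome figure only, independent outcomes.

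**Step 1: baseline check.** At ρ = 0 each coefficient test rejects in 4.8% to 5.2% of series, so the simulation reproduces the nominal 5%.

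**Step 2: multiplicity alone (ρ = 0).** Let p be the chance of at least one false positive in one patient's model. Over 6 patients the chance is 1 − (1 − p)^6.
- A-B-C model, 5 coefficients: p = 0.16, and 1 − 0.84^6 = 0.65. Separate runs gave 0.64 to 0.65.
- B-versus-C model (7/28 days), 3 coefficients, the most favourable reading: p is about 0.08, and the simulated chance over 6 patients is 0.39 to 0.40.
- A-B-C over both outcomes: 5 × 6 × 2 = 60 tests, 60 × 0.05 = 3.0 expected false positives, and 1 − 0.84^12 = 0.88 for at least one.
- SCED II, B-C-B-C, 7 coefficients: 0.19 to 0.24 per patient and 0.71 to 0.80 over 6 patients, depending on phase length.

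**Step 3: adding serial correlation.** Size of the nominal 5% test of the B-to-C level change, A-B-C model, 5/7/28 days:

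| ρ (assumed) | Size |
|---|---|
| 0 | 5% |
| 0.1 | 7% |
| 0.2 | 9% |
| 0.3 | 11% |
| 0.4 | 14% |
| 0.5 | 16% |
| 0.6 | 19% |

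For any of the 5 coefficients, the chance over 6 patients rises to 0.88 at ρ = 0.3 and 0.95 at 0.5. For the B-versus-C model it is 0.68 and 0.83. At ρ = 0.4, about 7 of the 60 tests are expected to be falsely significant, against 3.0 at the nominal level. The 24 tests of B-to-C level or slope (2 × 6 × 2) contribute about 3.3 of these, roughly half in the beneficial direction, against 24 × 0.05 = 1.2.

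**Step 4: what repairs it.**
- Bonferroni over 30 tests (5 × 6, one outcome) without modelling correlation (10/7/28 days) leaves a family-wise error of 0.038 at ρ = 0, 0.22 at 0.3 and 0.44 at 0.5. Adjusting the cutoff alone is not enough.
- Generalised least squares with ρ known restores 4.9% to 5.1% per coefficient. That is a best case.
- REML with ρ estimated gives about 6% to 7% for the B-to-C level test over ρ = 0 to 0.6. That run modelled follow-up as an added 12-day phase.
- A randomisation test of the B-to-C start, pooled over 6 SCED I patients, stays between 4.9% and 5.9% with 6 or 10 possible starts per patient. Those numbers of starts are assumed.

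**The case against.** The strongest reply is that the article is condensed and describes the regressions as a supplement. No stated rule turns one significant coefficient in one patient into a conclusion. Interpretation also rests on six visual features, Tau-U, a multilevel model in SCED I, and validation in new patients in SCED II. All of that stands, and it limits the consequence.

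Several stronger readings are tempting but not supported:
- A reader might infer that the plan declares days independent. It does not. It names a linear model with four kinds of parameter and is silent on the error structure. At ρ = 0 the individual tests hold their 5%, so the inflation per test depends on a correlation the article does not give.
- A reader might count 84 tests per experiment (7 × 6 × 2). For SCED I this treats follow-up as a modelled phase, which the listed contrasts do not include; 60 is the supportable count. Many of those concern the initial trend or Google Fit, not the training app.
- A reader might conclude that some training effect will be found whether or not the app works. That does not follow when the visual analysis leads.
- A reader might object that the intercept is defined at the start of the study. That does not prevent a test of B-to-C level or slope.
- A reader might call the unused randomisation an error throughout. It concerns SCED I only, and using it is an option. It also cannot rescue per-patient P values: with 10 equally likely starts, one patient's smallest possible P is 1/10 = 0.10.

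The reply does not remove the decision rule itself. The cutoff is stated and unadjusted, and it covers all per-patient trend, level and slope effects. The article exempts the moderator analysis from confirmatory P values but not these tests.

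**Conclusion.** The point holds in limited form and should be fixed before analysis. The multiplicity part needs no assumption about correlation: a chance of about 0.40 to 0.65 of at least one false positive among 6 SCED I patients per outcome, depending on whether the model covers B and C or A, B and C. The serial-correlation part is conditional: under positive correlation the intervals are too narrow, and the B-to-C level test has a size of about 9% to 19% for assumed ρ of 0.2 to 0.6. What is at stake is the labelling of effects as significant and their apparent precision.

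**What to change.** Change the analysis text and code as follows.
1. Fit the per-patient and multilevel piecewise models with AR(1) errors (REML or generalised least squares), and state this error structure.
2. Name the B-to-C change in physical activity as the one key contrast, and say beforehand whether it is the level change, the slope change or one stated combination. Report all other coefficients as estimates with intervals and no significance claim.
3. Optionally, in SCED I only, add a randomisation test pooled over patients, using the B-to-C start days that could have been drawn. The set of possible days must be recorded, since the article gives only minimum durations.

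No extra patients, visits or data are needed. The cost is wider intervals and fewer coefficients called significant. A small inflation remains (about 6% to 7% rather than 5%), because the correlation has to be estimated from short series.

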### Study Design

This study will be conducted using a series of 2 single-case experimental designs (SCEDs): a concurrent multiple-baseline design across participants (SCED I) [34,35] and an introduction/withdrawal design (SCED II). SCED is a family of high-quality experimental designs that can be used to draw causal inferences about the relationship between the intervention and the outcome [36,37]. In an SCED, the intervention is systematically manipulated across multiple phases of introduction and withdrawal while the outcome variable is measured repeatedly and frequently [36-38]. In this way, individual patients function as their own controls. An overview of both experiments according to the SCRIBE (Single-Case Reporting Guideline in Behavioral Interventions) guidelines [39] is provided in Table 1.

**Table 1 table1:** Single-Case Reporting Guideline in Behavioral Interventions design elements of single-case experimental designs (SCEDs) I and II.

	SCED I	SCED II
Design	Multiple baselines across participants	Introduction-withdrawal
Duration	52 days	Approximately 42 days (28-70 days)
Sequence of phases	A-B-C+follow-up	B-C-B-C
Description of phases	Phase A—baseline: 5 days minimum; no intervention, only monitoring of physical activity and self-control Phase B—Google Fit: 7 days minimum; only Google Fit intervention is administered Phase C—Google Fit+SCT^a^: 28 days minimum; Google Fit and SCT intervention are administered simultaneously Follow-up: 3 days minimum; no intervention, only monitoring of physical activity and self-control	Phase B—Google Fit: 7 days; only Google Fit intervention is administered Phase C—Google Fit+SCT: 7-28 days minimum; optimal phase length is determined from findings of SCED I; Google Fit and SCT intervention are administered simultaneously
Main outcomes	Average TACs^b^ per hour, measured continuously throughout the trial (at least 5 measures per phase) Daily self-control, measured twice daily throughout the trial (at least 5 measures per phase)	Average TACs per hour, measured continuously throughout the trial (at least 5 measures per phase) Daily self-control, measured twice daily throughout the trial (at least 5 measures per phase)
Randomization	Baseline duration is randomized with restriction to have at least 5 baseline observation days and 3 measurements	Not randomized

^a^SCT: self-control training.

^b^TAC: total activity count.

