The main aim of SCED II is to validate the effectiveness of the optimized intervention—in terms of duration and experience—based on the findings from SCED I. The design of SCED II is B-C-B-C, where, again, B refers to the physical activity intervention alone and C refers to the combination of physical activity intervention+SCT intervention. In both experiments, 6 participants will be monitored for at least one baseline phase and one intervention phase, with each phase lasting at least 5 data points following SCRIBE and What Works Clearinghouse guidelines [36,37,44]. Given that physical activity is measured continuously and self-control is measured twice a day, this will result in at least 28 data points during intervention phase C in SCED I and between 7 and 28 data points during intervention phase C in SCED II.

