### Participants

A total of 12 people with SMI will be recruited from the clinics of 2 large Dutch mental health care organizations: Dimence Groep and GGz Centraal. To meet quality standards, an SCED should include at least 3 participants [37,44,46]. To account for the high dropout rates common in the psychiatric population, we will include 6 participants in both SCEDs. Participants will receive €50.00 (US $56.00) for taking part. To promote continued commitment to the longitudinal design, participants will receive €10.00 (US $11.00) at the start, €20.00 (US $22.50) midway, and €20.00 (US $22.50) at the end of the study.

Participants need to meet the inclusion criterion of having an SMI, including but not limited to schizophrenia, bipolar disorder, and major depression, following the Dutch consensus definition of SMI [47]: (1) requires treatment (ie, no symptomatic remission), (2) is associated with severe limitations in social or societal functioning (ie, no functional remission) that result in and are caused by a psychiatric disorder, (3) is not transient (ie, is structural, chronic, or long-term [at least several years]), and (4) requires coordinated care from professional caregivers in care networks to realize the treatment plan.

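### SCED II, the validating experiment, gets no combined B-versus-C estimate across its six patients, because the multilevel piecewise model is confined to SCED I

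*Protocol article*

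**What the plan says.** The Study Design section separates the two experiments. SCED I explores initial effectiveness, moderators and duration. For SCED II, "The main aim of SCED II is to validate the effectiveness of the optimized intervention", using a B-C-B-C sequence in new patients. Under Participants, "we will include 6 participants in both SCEDs". Table 1 fixes the first and third phases of SCED II ("Phase B—Google Fit: 7 days; only Google Fit intervention is administered"), and the text allows "between 7 and 28 data points during intervention phase C in SCED II".

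The Visual Analysis section makes visual reading the main mode of interpretation. It adds Tau-U as the nonoverlap index and names B versus C as the SCED II contrast. For SCED II it also adds a consistency check between the two B phases and between the two C phases.

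The Piecewise Linear Regression Analysis section presents the regression as a supplement. It describes the model as follows: "The PLM model calculates 4 parameters (intercept, trend, level, and slope) separately for data from each phase". It then says "Using the PLM, we will construct a linear model for each individual patient" and "We will use a cutoff of *P*<.05 to determine significant effects". Aggregation is limited: "In SCED I only, we will also construct a multilevel PLM to aggregate single-case findings across all participants included". The same paragraph credits aggregation with better external validity and overall trend, level and slope effects, and uses its random slopes to explore moderators.

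**The concern.** The benefit the article claims for aggregation, an overall effect with better external validity, is what a validating experiment needs, yet only the exploratory experiment gets it. Sample size does not explain the difference, since both experiments have six patients and the same two outcomes. SCED II even has two introductions of SCT per patient, against one in SCED I. Moderator exploration explains why a multilevel model is used in SCED I, but not why the overall effect is left out of SCED II.

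This is an explicit exclusion rather than a detail left to a fuller document. As written, SCED II offers no single figure for how much SCT adds to Google Fit and how uncertain that is. The regression reader gets six sets of P values, with no stated rule for reading them together.

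**Working it through.** **Inputs from the article.** Six patients; B = 7 days; C = 7, 14, 21 or 28 days; sequence B-C-B-C; threshold P<.05. As a check on the layout, 7 + c + 7 + c gives 28, 42, 56 and 70 days. This reproduces the stated SCED II duration of about 42 days (28-70).

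**Assumptions not in the article.** Two-sided tests; daily errors with within-patient SD 1; no missing days; a constant level shift of 0.5 or 1 SD while SCT is on, common to all patients unless stated. Errors are independent, then lag-1 autocorrelated at 0.3.

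**Two codings.** (a) Trend plus a level and a slope change at each switch (8 parameters), the closer reading of the regression section. (b) Intercept, trend and one B-versus-C level term over both phase pairs (3 parameters), closer to the contrast named under Visual Analysis.

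**Formulas.**
- Single patient: SE = sqrt(a'(X'X)⁻¹a), and power is from the noncentral t with n − p df and noncentrality δ/SE. Coding (a) tests the first B-to-C level change.
- Pooled: SE = SE(patient estimate)/√6, noncentral t with 5 df. In coding (a) the patient estimate averages both introductions. This t test on six patient estimates stands in for the multilevel model.

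| Coding, C days | Single SE | Power at 0.5 / 1 SD | Pooled SE | Power at 0.5 / 1 SD |
|---|---|---|---|---|
| (a) 7 | 1.09 | 7% / 14% | 0.768/√6 = 0.313 | 26% / 72% |
| (a) 14 | 0.99 | 8% / 17% | 0.697/√6 = 0.285 | 30% / 80% |
| (a) 28 | 0.92 | 8% / 19% | 0.652/√6 = 0.266 | 33% / 85% |
| (b) 7 | 0.42 | 21% / 63% | 0.419/√6 = 0.171 | 65% / >99% |
| (b) 14 | 0.36 | 28% / 78% | 0.359/√6 = 0.146 | 78% / >99% |
| (b) 28 | 0.32 | 34% / 87% | 0.319/√6 = 0.130 | 86% / >99% |

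**Where the gain in (a) comes from.** Part is the averaging of two introductions. Pooling the first introduction alone, with a between-patient SD of 0.3 in the effect, gives only 15-17% at 0.5 SD and 41-53% at 1 SD.

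**Effect varying between patients (SD 0.5).** The pooled SE becomes sqrt(SE² + 0.25/6). Pooled power is then 19-23% and 58-67% under (a), and 33-39% and 85 to about 90% under (b).

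**Width of the interval.** Half-width is about 2.571 × SE. Under (b) with a common effect this is 0.44, 0.38 and 0.33 SD for C = 7, 14 and 28. With between-patient SD 0.5 and C = 7 it is 2.571 × sqrt(0.171² + 0.0417) = 0.69 SD.

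**Autocorrelation 0.3, no effect (simulation).** Single-patient false positives are about 11% under (a) and 13% under (b), because ordinary least squares ignores the dependence. The t test on six patient estimates stays at about 5% under both.

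**The case against.** The strongest reply is that a single-case experiment does not live by pooled P values. Visual analysis is primary, Tau-U and the consistency check apply to SCED II, and the regression is declared a supplement. Patients act as their own controls, the sample is deliberately heterogeneous, and replication across cases is the basis of inference. Leaving six such patients unpooled is a known and defensible choice, and the multilevel model has a visible purpose in SCED I, namely moderators.

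Most of this stands. Three stronger readings that a reader might infer are not supported:

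- *That SCED II rests only on single-patient tests.* It does not; only its regression evidence does.
- *That these tests cannot tell an effect from no effect.* This holds at 0.5 SD under coding (a), but not generally. Under coding (b), with independent errors and a common 1 SD effect, three or more of six patients are significant in 86-99.7% of trials, against under 1% with no effect. Nor does the article say that one significant term in one patient would count as validation, so a chance count over all terms is not its criterion.
- *That pooling cures the problem.* At 0.5 SD, coding (a) still gives only 26-33% power after pooling.

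A fair objection also applies to one possible remedy. The level jump at each switch would miss an effect that builds up, and the article leaves open whether SCT effects are immediate or cumulative.

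What the reply does not supply is a reason for withholding from SCED II a summary that the article itself values. Adding it displaces nothing in the visual analysis.

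**Conclusion.** The point holds as a weakness of the analysis choice, not as a contradiction: the validating experiment has no stated combined B-versus-C estimate or confidence interval, and no reason is given. Under both codings examined, pooling raised power over the single-patient test. The gain was from 14-19% to 72-85% at 1 SD with separate terms at each switch, and from 21-34% to 65-86% at 0.5 SD with one contrast. A test on the six patient estimates also kept its error rate near 5% under modest autocorrelation, while single-patient tests roughly doubled theirs.

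These sizes rest on assumed effects, autocorrelation, complete data and model coding. The direction is secure; the amounts are illustrative. The change is worth making, but SCED II is not uninterpretable without it.

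**What to change.** In the Piecewise Linear Regression Analysis section, lift the restriction to SCED I for the overall effect and fit the multilevel model to SCED II as well, still as a supplement to the visual analysis. Specify:

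- one B-versus-C condition contrast over both phase pairs as the summary estimate, separately for physical activity and self-control;
- the slope effect reported beside it, so that a cumulative effect is not missed;
- a 95% confidence interval based on between-patient variation (six patients, 5 df);
- the first introduction shown separately, because carryover of SCT into the second B phase would dilute the combined contrast;
- moderator exploration kept in SCED I.

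The cost is one more run of a model and package already planned, with no new data or patient burden. The drawback is a wide interval from six heterogeneous patients, wider still with dropout, which should be said in advance. The Results section reports six of the twelve planned participants included. It does not say in which experiment, but the estimate may still be fixable before SCED II data are seen.
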